## Abstract

**Abstract:**

**Introduction:**

Ear, nose and throat (ENT) conditions are highly prevalent in primary and secondary care, yet patients frequently face prolonged waits for specialist review. In England, over half of ENT patients wait beyond the NHS 18-week referral-to-treatment target. Many of these cases can be effectively managed with advice and non-surgical interventions, presenting an opportunity for remote service innovation.

This study aims to evaluate the clinical effectiveness, cost-effectiveness, acceptability and environmental sustainability of a digitally enabled remote ENT clinic model compared with traditional face-to-face pathways.

**Methods and analysis:**

This single-centre, mixed-methods, prospective cohort study will be conducted at University Hospitals Birmingham NHS Foundation Trust. Remote clinics will use trained staff to collect diagnostic data (including endoscopic imaging and boothless hearing tests) for consultant review via secure cloud-based software. Quantitative analysis will assess patient outcomes, costs, waiting times, carbon footprint and satisfaction. Qualitative data from semi-structured interviews with patients, clinicians and managers will explore acceptability, scalability and barriers to implementation. The qualitative data will be analysed using the framework methodology, according to the non-adoption, abandonment, scale-up, spread and sustainability framework, while the strengthening the reporting of observational studies in epidemiology framework will be used to guide the reporting of quantitative data. Cost-effectiveness analyses will follow NICE guidelines, while environmental impact will be measurement will be informed by the sustainability in quality improvement framework. Recruitment will be aiming for 300 completed datasets and 30–35 interviews.

**Ethics and dissemination:**

Ethical approval has been granted (IRAS 350908; REC 25/SW/0116). Findings will be disseminated via conferences, peer-reviewed journals and institutional communication channels.

STRENGTHS AND LIMITATIONS OF THIS STUDYMixed methodology analysis: holistic capture of different types of data reflecting the wider impact and ramifications of the implementation of remote specialist clinics.Real-world implementation: data is captured in real-world settings, allowing study of the challenges of providing a service away from a controlled environment.Study site characteristics: the study sites offer hundreds of ear, nose and throat clinical encounters per week, facilitating data capture for a high volume and diverse population of patients.Selection bias: the study takes place in a single multi-centre NHS Trust, and therefore runs a risk of potentially excluding patients of particular demographics that do not attend that Trust.

## Introduction

 In 2009 the NHS Constitution set the standard of 92% of patients waiting no longer than 18 weeks from referral to treatment.^1^ In December 2024, 7.5 million patients in England were waiting for an appointment, with more than two-fifths waiting beyond the NHS standard.^2^ That proportion varies by speciality, with ear, nose and throat (ENT) demonstrating the worst waiting times, with over half of the patients exceeding the 18-week target.^1^

Hearing and ear problems, alongside nasal symptoms, are common in primary and secondary healthcare, with ear pain, discharge, recurrent infections, chronic rhinosinusitis and allergic rhinitis particularly common. While primary care management may suffice, many patients need specialist ENT referrals for diagnosis and management. However, lengthy waits, often exceeding twelve months, are commonplace for specialist consultations.^3^ This equates to over half a million patients having increased time spent with disease, distress and also potentially a poorer prognosis. Recent evidence suggests ENT patients are more commonly managed with advice, medications and then discharge, when compared with specialities such as orthopaedics or gynaecology with a higher proportion converting to surgical intervention,^4^ indicating that they can be effectively managed with fewer appointments and occasionally, entirely remotely.

Responding to the delays facing patients, a digitally empowered, remote ENT system has been developed by our team of collaborators, capitalising on advances in endoscopic nasal and ear imaging and boothless hearing tests. A pilot study, comprising 53 patients, demonstrated that 83% of cases could be effectively managed remotely via this service, with high levels of satisfaction reported by both patients and general practitioners.^5^

The remote service uses trained nursing or physician associate staff to ‘collect’ the necessary patient data, for example, supervision of tablet history collection and boothless audiogram, and perform video of patient ears/nose, thereby allowing consultants to review this information and diagnose and manage patients remotely (figure 1). Audiometric testing will be performed using calibrated boothless audiometers developed by hearX Group (Pretoria, Gauteng, South Africa). These devices are commercially available systems that meet the required regulatory and calibration international standards for clinical use (ISO 8253-1/ISO 389 Series/IEC 60 645-1/ANSI S3.6) and are CE-marked registered and certified in Europe. The company’s regulatory standards are available in detail on their webpage: https://www.hearxgroup.com/products/heartest. This enables optimisation of resources through face-to-face, technician-delivered clinics in varied locations with consultants providing opinions flexibly. The service can be placed in different locations, closer to the patients, reducing travel and environmental impact. The University Hospitals Birmingham (UHB) NHS Foundation Trust has approved the introduction of this novel pathway into their outpatient referral pathway from primary to secondary care, currently facilitating the delivery of Otology and Rhinology clinics.

**Figure 1 F1:**
[figure not shown]
Traditional and remote clinic pathways infographic. ENT, ear, nose and throat.

Our team has conducted a review of the literature to inform and guide the design of this study.^6^ Despite evidence supporting the feasibility and safety of digitally enabled remote ENT clinics, no consensus exists on the ideal placement of such a service. Moreover, there is still a need to further understand this pathway’s real-world effectiveness and acceptability across different stakeholders (patients, clinicians, managers), compared with the traditional face-to-face consultation model. Moreover, we need to investigate whether there are any specific groups of patients that such a digitally empowered pathway would work better for compared with others. Furthermore, aligning with the NHS net-zero agenda, we need to understand whether RAPID ENT could contribute to the reduction of the carbon footprint of the ENT outpatient care delivery.

Our research focus will evaluate the clinical and cost-effectiveness, acceptability and environmental sustainability of the remote clinics model, compared with the traditional pathway. This study is due to launch in October 2025 and will be undertaken for a period of up to 2 years, with October 2027 being defined as the end date of the study. The end of the study will be the date of the last follow-up and data collection via questionnaires and interviews of patient-participants, post the completion of their treatment. Documents will be archived following the University of Birmingham (UoB) Code of Practice for Research.

## Methods and analysis

### Project setting

The study will be conducted across hospital and primary care outpatient clinics offered by UHB. Data will be collected from patients following all permutations of the remote pathway alongside standard ENT outpatient clinics, such as hospital outpatients, diagnostic hubs and primary care clinics. During appointments, patient data captured via the Endoscope-I software will be stored securely. Post-consultation, data will be transmitted through an encrypted cloud service and reviewed by ENT Consultants using secure, bespoke app-based software. Following completion of their outpatient pathway, consented patients will be asked to complete a follow-up questionnaire, and some will be invited to a semi-structured interview.

### Primary outcome

#### Clinical efficiency

Assess the proportion of patients who can be successfully diagnosed and managed remotely and calculate the number of appointments required to reach definitive treatment. We define “successful remote management” as patients with a diagnosis and treatment plan decided after a single remote consultation, without further appointments required to reach diagnosis/initial management. Further follow-up appointments that were required as part of further investigations or treatment do not constitute a “failed remote management” unless diagnosis was not reached after the initial appointment. Assess re-presentation rates to the ENT services for patients that attended the remote clinics.

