This is an observational study, and we are not measuring the effect of an intervention. Our initial sample size calculations have been driven by similar pieces of implementation studies in the literature, looking into studies assessing non-inferiority interventions for remote/telehealth clinics, as well as assessing the potential financial benefit to the patients/service and the environmental impact,^11^,^15^ further informed by similar studies mapped through our team’s scoping review.^6^ Continuous sampling will be undertaken on both pathways until we reach a number of 150 participants from each group that have completed the initial questionnaires. The patients of the remote pathway will also be sent a follow-up questionnaire after their discharge, asking for their overall experience of the new service. The total of recruited participants will be expected to exceed the minimum of 300 we need for our analysis, and we will be allowing for a 10% attrition, as the current number for patients seen in face-to-face and remote clinics exceeds the 80 patients per cohort, per week. All the primary outcomes data will be extracted directly from the clinical notes of the patients, while the data of the secondary outcomes will be procured via questionnaires.

For the interviews, we will use a topic guide developed based on the existing literature and the research team’s experience of technology and innovation implementation, as well as service redesign.^16^,^18^ Through the interview process, we will investigate the experience of the different stakeholders involved in the remote pathway. We will undertake purposive sampling to select participants, expecting 30–35 participants in total, to allow for thematic saturation to take place.^19 20^ Participants in the interviews will be classified into two categories: patient participants and NHS staff. Recruitment will continue until overall thematic saturation has been achieved within each group. Patients enrolled will be approached, after completing the remote clinic pathway, while clinicians, managers and the other stakeholders will be given participation leaflets and invited via email or in person to participate in the study through interviews. If non-English speakers participate in the interviews, interpreters will also be facilitating the process.

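### Two of the three primary measures, single-consultation success and re-presentation, are worded for remote patients only and cannot contribute to the stated comparison with face-to-face care

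*Protocol article*

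**What the plan says.** The Abstract states the aim as an evaluation of the remote model "compared with traditional face-to-face pathways". The last part of the Introduction repeats it: the study will evaluate "clinical and cost-effectiveness, acceptability and environmental sustainability of the remote clinics model, compared with the traditional pathway". Under Recruitment, sampling continues on both pathways "until we reach a number of 150 participants from each group".

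The section Primary outcome, Clinical efficiency, holds three measures:

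1. Success: "Assess the proportion of patients who can be successfully diagnosed and managed remotely". The definition that follows requires a "diagnosis and treatment plan decided after a single remote consultation".
2. Appointments: "calculate the number of appointments required to reach definitive treatment". No group is named.
3. Re-presentation: "Assess re-presentation rates to the ENT services for patients that attended the remote clinics".

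On the data source, Recruitment says: "All the primary outcomes data will be extracted directly from the clinical notes of the patients". This is not limited to one pathway. The Quantitative analysis section plans regression models between groups, count models with number of appointments as the example, and time-to-event models for time to a definitive decision or treatment. It also plans covariate adjustment, with propensity score weighting as a robustness check.

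**The concern.** A face-to-face patient cannot meet a success definition that requires a remote consultation, and a face-to-face patient who comes back is outside the re-presentation item. Yet face-to-face visits may also end without a diagnosis and plan, and those patients may also return. A remote rate on its own does not show whether the remote pathway does better, the same or worse than usual care on these two measures.

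Number of appointments does not fully fill the gap. A pathway that discharges early can show fewer appointments while more of its patients return, and only re-presentation measured on both sides would reveal that. Nor is a low appointment count the same as success as defined here, because the protocol does not count later visits for investigation or treatment as failures once a diagnosis has been reached.

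**Working it through.** **Which measure can be compared**

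| Primary measure | Group in the wording | Face-to-face counterpart | Between-group estimate |
|---|---|---|---|
| Single-consultation success | Remote | None given | No |
| Number of appointments | Not restricted | Same measure applies | Yes; a count model is planned |
| Re-presentation | Remote | None given | No |

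The limit lies in the wording of the first and third measures, not in the data source, since primary data come from clinical notes.

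**Inputs**

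- n = 150 per group (Recruitment).
- Remote success of 83%, from the 53-patient pilot (Introduction). The protocol does not state this as a design input.
- Face-to-face success of 70%, 83% or 95%, and re-presentation of 10% (range 5% to 20%). These are assumptions; the document gives no such figures.

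The only part of the plan's sample size that can be reproduced is 2 × 150 = 300. No significance level, power, effect size or margin is stated to check further.

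**As written: one group**

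1.96 × √(p(1−p)/n) = 1.96 × √(0.83 × 0.17/150) = 0.060, so 83% ± 6.0 points.

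If the face-to-face rate were 70%, remote would be 83 − 70 = 13 points better. If it were 95%, remote would be 95 − 83 = 12 points worse. The success measure would read 83% in both cases.

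**If measured in both groups**

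Half-width = 1.96 × √(p₁(1−p₁)/150 + p₂(1−p₂)/150), with p₁ = 0.83:

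- p₂ = 0.70: 1.96 × √(0.1411/150 + 0.2100/150) = 0.095, or 9.5 points.
- p₂ = 0.83: 1.96 × √(2 × 0.1411/150) = 0.085, or 8.5 points.
- p₂ = 0.95: 1.96 × √(0.1411/150 + 0.0475/150) = 0.0695, or about 7 points.

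Re-presentation at 10% in both groups: 1.96 × √(2 × 0.10 × 0.90/150) = 0.068, or 6.8 points. Over 5% to 20% the range is 4.9 to 9.1 points.

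At two-sided 5%, 150 per group gives about 92% power to separate 83% from 95%, and about 43% to separate 83% from 90%. The comparison would therefore be informative for large differences and uncertain for small ones. All these figures are unadjusted; covariate adjustment or weighting would change them.

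**The case against.** **The primary outcome still compares.** A reader might infer that the primary outcome as a whole cannot answer the comparative question. The document does not support that. Number of appointments is a primary measure without a group restriction, and it has a count model in a section that compares groups. The time-to-event model for reaching a definitive decision or treatment would also carry part of the contrast between a 70% and a 95% face-to-face rate, though not all of it. Waiting times, costs and carbon footprint add secondary comparisons.

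**Unequal follow-up is not ignored.** A reader might also infer that patients discharged late simply have less time to re-present and that nothing is done about it. The Quantitative analysis section plans Cox models for differential follow-up. It ties them to differences across pathology and not expressly to re-presentation, so the match is imperfect. The exact window is also a detail that an article commonly leaves to the full protocol. The absence of a stated window is therefore not part of this point.

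**The proportion manageable remotely is a legitimate quantity.** It mirrors the pilot's 83% and has meaning only in remote patients. This stands, and it is a reason to keep that proportion as a descriptive result. The statement that the study is observational and not measuring an intervention's effect does not remove the comparator, because the aim, the recruitment target and the analysis section all assume one.

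**Figure 2 is not visible here.** It concerns data capture points in both pathways and might show that equivalent information is collected from traditional patients. Even so, the text defines these two measures for the remote group alone, and it is the text that needs changing.

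**Conclusion.** The point holds in this form: two of the three primary measures are defined for the remote group alone and cannot contribute to the comparison that the study sets out to make. Only number of appointments can support a primary between-group comparison.

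The consequence is a remote success rate known to about ± 6.0 points with no comparator, where the planned sample could give a difference with a half-width of about 7 to 9.5 points (8.5 if both rates are 83%). For re-presentation, a difference with a half-width of about 6.8 points is forgone at an assumed 10% rate. The remote figure rests on the pilot's 83%, and every face-to-face and re-presentation rate is an assumption. The finding about the definitions depends on none of these numbers.

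**What to change.** 1. Define success in a pathway-neutral way: diagnosis and initial management plan reached after the first consultation, whether remote or face-to-face.
2. Extract success and re-presentation from the clinical notes of both groups. Report adjusted between-pathway differences, using the covariates and propensity weighting already listed under Quantitative analysis.
3. Measure re-presentation from the same origin in both groups, such as discharge, with either a common window or the time-to-event methods already planned. Counting from first appointment would be a poor choice: patients on longer pathways would have less time at risk after discharge, and pathway length may itself differ between the groups.
4. Keep the remote-only proportion as a descriptive feasibility result.

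The minimum alternative is to label the two remote-only items descriptive and name number of appointments as the comparative primary outcome. Either choice should be written down before outcomes are extracted.

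The cost is a change of wording and modest extra extraction for 150 traditional patients, whose notes would already be read if number of appointments is compared. The remote-only second questionnaire is no obstacle, since primary data do not come from it. Follow-up for re-presentation must be completed or censored by the October 2027 end date.

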### Secondary outcomes

Clinical throughput impact:Investigate impact of remote pathway on waiting times from referral to treatment.Compare the clinician time required per remote consultation to reach diagnosis/definitive treatment.Stakeholder acceptability:Examine barriers to implementation, training needs, scalability and throughput.Determine the optimal setting for data capture and assess geographic variation.Assess the impact across different demographics, especially under-served populations.Health economic analysis:Conduct a cost-consequences analysis detailing waiting times, quality of life, resource use, costs, time off work and productivity for both study groups.Perform cost-consequence and cost-utility analyses from an NHS perspective.Environmental sustainability:Calculate the direct (patient journey) and indirect (clinic output) carbon footprint of the ENT outpatient service by assessing carbon dioxide equivalents (CO_2_Eq) for both new and existing clinic models by location.

### Theoretical framework

The remote pathway implementation will be informed by the non-adoption, abandonment, scale-up, spread and sustainability (NASSS) framework, developed to support, guide and monitor the implementation of digital technologies in health and social care.^7^ The NASSS framework uses seven domains to describe various aspects of the technology, end users, organisational structure and broader policy-driven context.^8^ The principles of a single centre prospective cohort study will be followed according to the STROBE statement^9^ for quantitative data analysis. We will measure the environmental impact of the remote clinic service, the Centre for Sustainable Healthcare’s sustainability in quality improvement (SusQI) framework^10^ that aligns with our aim of embedding principles of sustainable practices within healthcare.

### Inclusion criteria

Patient participants: patients referred from primary care, adults (18 years of age or older), with conditions of the ears or nose.

Non-patient participants: stakeholders with previous or current experience in digital or service transformation, stakeholders engaging in the implementation or delivery of the remote-enabled ENT clinical service.

### Exclusion criteria

Patient participants: patients referred for tertiary assessment, and patients with suspected cancer, patients younger than 18 years old. Patients with balance or vertigo problems as their primary presentation.

Non-patient participants: stakeholders without previous or current experience in remote services, stakeholders without understanding or knowledge of ENT clinic service delivery or design.

### Recruitment

Patients referred from primary care to ENT specialist services and attending either a conventional face-to-face consultant-led clinic or a remote clinic will be recruited into the study. We will send an invitation letter explaining the purpose of the study to the patients, along with their clinic invitation letter, and potential participants will be approached prior to their initial clinic appointment.

On their attendance at clinic, patients will be approached by a member of the healthcare team and will be given the study information package and offered the opportunity to ask questions and discuss their potential participation in the study. For those patients who agree to take part, this will be documented in their medical records and the research team will begin informed consent procedures.

Patients will not be randomised, and the study will not have any influence on the allocation of patients to the traditional or the remote pathway, which will be arranged by UHB, on a weekly basis, according to clinical priority and waiting length per referral. The clinic allocation process is regulated by the hospital and patients are allocated in consecutive order to either a face-to-face or a remote clinic, until all the slots of that week have been filled, before booking patients for a different week. Patient prioritisation is made in the form of urgency, without reference to the method of clinic delivery. Patient demographics, disease severity or other characteristics are not used in regards to allocation to an in-person or remote clinic appointment.

This will ensure that selection bias will not be introduced on the patients seen in the remote pathway, compared with the cohort seen face-to-face. We will assess propensity scores for the patients and assess their propensity score weighting using logistic regression.

This is an observational study, and we are not measuring the effect of an intervention. Our initial sample size calculations have been driven by similar pieces of implementation studies in the literature, looking into studies assessing non-inferiority interventions for remote/telehealth clinics, as well as assessing the potential financial benefit to the patients/service and the environmental impact,^11^,^15^ further informed by similar studies mapped through our team’s scoping review.^6^ Continuous sampling will be undertaken on both pathways until we reach a number of 150 participants from each group that have completed the initial questionnaires. The patients of the remote pathway will also be sent a follow-up questionnaire after their discharge, asking for their overall experience of the new service. The total of recruited participants will be expected to exceed the minimum of 300 we need for our analysis, and we will be allowing for a 10% attrition, as the current number for patients seen in face-to-face and remote clinics exceeds the 80 patients per cohort, per week. All the primary outcomes data will be extracted directly from the clinical notes of the patients, while the data of the secondary outcomes will be procured via questionnaires.

For the interviews, we will use a topic guide developed based on the existing literature and the research team’s experience of technology and innovation implementation, as well as service redesign.^16^,^18^ Through the interview process, we will investigate the experience of the different stakeholders involved in the remote pathway. We will undertake purposive sampling to select participants, expecting 30–35 participants in total, to allow for thematic saturation to take place.^19 20^ Participants in the interviews will be classified into two categories: patient participants and NHS staff. Recruitment will continue until overall thematic saturation has been achieved within each group. Patients enrolled will be approached, after completing the remote clinic pathway, while clinicians, managers and the other stakeholders will be given participation leaflets and invited via email or in person to participate in the study through interviews. If non-English speakers participate in the interviews, interpreters will also be facilitating the process.

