### Quantitative methodology

Quantitative methodology study process using questionnaires (figure 2):

Patients attending traditional pathway and new remote pathway recruited.Remote pathway participants: two questionnaires - first on the day of clinic attendance and second after completion of treatment or discharge.Traditional pathway participants: one questionnaire on the day of clinic attendance.

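### The claim that selection bias is excluded among patients seen rests on a rule that is neutral only at booking, while patients enter and are grouped by attendance

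*Protocol article*

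**What the plan says.** Under Recruitment, the hospital controls allocation. Patients are not randomised; "patients are allocated in consecutive order to either a face-to-face or a remote clinic" until the week's slots are full, and the text states that demographics, severity and other characteristics play no part. From this the section concludes: "This will ensure that selection bias will not be introduced on the patients seen in the remote pathway, compared with the cohort seen face-to-face".

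Entry to the study is defined differently. Those recruited are patients "attending either a conventional face-to-face consultant-led clinic or a remote clinic will be recruited into the study". An invitation letter goes out with the clinic letter, but the consent process starts later: "On their attendance at clinic, patients will be approached by a member of the healthcare team". Sampling then continues "until we reach a number of 150 participants from each group that have completed the initial questionnaires", and Quantitative methodology places that questionnaire on the day of clinic attendance. The same section forms the groups by attendance: "Patients attending traditional pathway and new remote pathway recruited".

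Recruitment mentions propensity scores. Quantitative analysis adjusts for age, sex, deprivation quintile, baseline symptoms, condition category, comorbidity count and distance to clinic, with propensity score weighting as a robustness check. The strengths and limitations list acknowledges selection bias only for people who do not attend this Trust.

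**The concern.** The argument for comparability concerns who is booked where. The groups compared are those who attended, consented and completed a questionnaire. Between booking and entry, a patient who knows the clinic type may decline, fail to attend or, if the service permits it, move to the other clinic. The booking rule governs none of these steps. If they depend on both the pathway and the patient's prognosis, the groups differ at entry, although the protocol states that this cannot happen.

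Three things are at stake:

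- **Between-group comparisons.** Number of appointments and time to decision or treatment rely on comparable groups.
- **The remote success proportion in the primary outcome.** Patients who refuse or miss a remote slot are not in its denominator.
- **The secondary objectives on barriers, throughput and under-served populations.** Refusal and non-attendance are direct evidence for these, and a cohort entered at attendance does not observe them.

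**Working it through.** **The plan's own figure.** The only related figure is the sample size: 2 × 150 = 300, which agrees with the stated minimum. The plan also says "we will be allowing for a 10% attrition"; 150 / 0.90 = 166.7, so 167 per group or 334 in total. Such an allowance protects the number of patients. It says nothing about whether losses are alike in the two pathways.

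**Inputs.** The document gives no rate of declining, non-attendance or switching. All rates and means below are therefore assumptions that show the mechanism, not estimates for this service. Neither illustration includes the planned adjustment.

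**Illustration 1: switching before the first appointment.** Assume 100 patients booked to each pathway, no true pathway effect, a mean of 2.5 appointments for complex patients and 1.6 for others, and c complex patients per 100 in each booked group. A fraction s of the complex patients booked to remote attend face-to-face instead, and nobody else moves.

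- Remote mean = [(100 − c) × 1.6 + c(1 − s) × 2.5] / (100 − cs)
- Face-to-face mean = [(100 − c) × 1.6 + c(1 + s) × 2.5] / (100 + cs)

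| c | s | Remote, by attendance | Face-to-face, by attendance | Spurious difference |
|---|---|---|---|---|
| 10 | 20% | (144 + 20)/98 = 1.673 | (144 + 30)/102 = 1.706 | 0.03 |
| 10 | 50% | (144 + 12.5)/95 = 1.647 | (144 + 37.5)/105 = 1.729 | 0.08 |
| 10 | 100% | 144/90 = 1.600 | (144 + 50)/110 = 1.764 | 0.16 |
| 5 | 20% | (152 + 10)/99 = 1.636 | (152 + 15)/101 = 1.653 | 0.02 |
| 5 | 100% | 152/95 = 1.600 | (152 + 25)/105 = 1.686 | 0.09 |

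Grouped by booked pathway, both means are 1.69 (c = 10) or 1.645 (c = 5), and the difference is 0 in every row.

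**Illustration 2: declining or non-attendance.** Assume that a prognostic trait is present in 40% of those booked to each pathway and shifts the outcome by 30 percentage points. Everyone enters at 80%, except trait carriers booked to remote, who enter at rate r.

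- Trait share among remote entrants = 0.4r / (0.4r + 0.6 × 0.8)
- Spurious difference = 30 × (0.40 − that share)

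| r | Remote trait share | Face-to-face trait share | Spurious difference (points) |
|---|---|---|---|
| 80% | 40.0% | 40% | 0 |
| 70% | 36.8% | 40% | 0.9 |
| 60% | 33.3% | 40% | 2.0 |
| 50% | 29.4% | 40% | 3.2 |
| 40% | 25.0% | 40% | 4.5 |

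Regrouping by booked pathway does not change these figures, because the missing patients have no study data.

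In both illustrations booking is perfectly balanced and the attending groups are not. The bias vanishes when loss and movement are unrelated to pathway or to prognosis.

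**The case against.** The case on the other side is substantial.

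- **Switching is not documented.** A reader might infer that patients do move between clinics and so break the allocation. The protocol does not say that they may, and it describes allocation as regulated by the hospital. Only the conditional statement is supported. It also applies only before the first appointment: a remote patient who needs a further appointment to reach diagnosis counts as a failure under the primary outcome definition and is not lost.
- **Digital confidence is a weaker driver than it sounds.** The Introduction describes clinics that patients attend in person, where staff supervise the tablet history and hearing test. Nothing in the document shows that digital confidence determines attendance.
- **Adjustment is planned.** Symptoms, condition, comorbidity and distance cover complexity and severity at least in part, and propensity weighting is added. This stands. What remains is unmeasured preference and the patients who never enter.
- **The direction is not fixed.** A reader might infer that the bias favours the remote model. That follows from the pattern assumed above; selective non-attendance at face-to-face clinics could reverse it.
- **Regrouping is not a full cure.** It corrects switching only. Nor does it give a contrast for the within-remote measures, namely the success proportion and re-presentation.
- **Enrolling attenders is ordinary in an observational cohort, and an article may leave booking fields and flow counts to the full protocol.** That is fair, and their absence is not the point. The article states both the entry rule and a categorical conclusion, and the conclusion does not follow from the rule.

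**Conclusion.** The point holds in a limited form. Neutral booking supports comparability of the patients booked, not of those who attended, consented and completed the first questionnaire. The assurance about patients seen is therefore unsupported, and the limitations list does not acknowledge this route.

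The size cannot be established from the document. With 10% complex patients and the assumed means, the unadjusted spurious difference runs from about 0.03 appointments (20% of complex patients booked to remote switching) to 0.16 (all of them, which is the extreme case). Under the differential-entry assumptions it runs from 0 to 4.5 percentage points. The planned adjustment would reduce these figures by an amount that cannot be stated. The claim that the comparison is biased, or biased in favour of the remote model, goes further than the document allows.

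**What to change.** 1. Limit the assurance in Recruitment to booking: allocation does not use patient characteristics, but the patients who attend and consent may still differ between pathways. Add this to the limitations.
2. Record for each participant the pathway first booked as well as the pathway attended. If any participant switched, compare the groups by booked pathway and give the comparison by attended pathway as a sensitivity analysis. State that this deals with switching only.
3. Obtain from the hospital booking system anonymous counts, by booked pathway, of eligible patients booked, declined, not attended and switched. Report them to show whether loss was differential, and as evidence for the acceptability and throughput objectives.
4. Report the proportion successfully managed remotely as a proportion of attenders, alongside those counts.

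The cost is one extra field and one aggregate extract; since the hospital makes the bookings, the data should already exist. If many patients switch, the booked-pathway contrast is slightly diluted.
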